**Methods:**

This randomized controlled trial will randomize 1330 women to control or intervention groups in 3 regions of different socioeconomic status. Women will be recruited from clinical and social media sites. The intervention group will be provided with access to the Eating4Two mobile phone app which provides nutrition and dietary information specifically tailored for pregnancy, advice on food serving sizes, and a graph that illustrates women’s weight change in relation to the range recommended by the Institute of Medicine. Women will be encouraged to use the app to prompt conversations with their maternity care providers about weight gain in pregnancy. The control group will receive routine antenatal care.

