## Methods

### Study Design and Overview

This study is an unblinded, 2-armed randomized control trial that will test the primary hypothesis that a greater proportion of women in the intervention group compared with the control group will limit GWG within the range recommended by the IOM. We will randomize 1330 pregnant women to the control and intervention groups. Those in the control group will receive usual antenatal care, and those in the intervention group will receive usual care augmented with the smartphone app. Participants allocated to the intervention group are prompted by the smartphone app to discuss weight changes with their maternity or health care provider. The researcher responsible for analyzing the data will be blind to group allocation.

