### Recruitment and Randomization

Recruitment will be via social media and health professionals providing antenatal care or childbirth education. Social media will publish the research aims and eligibility criteria and invite potential participants to contact the research assistant who will provide more information and a research information pack. Health professionals will introduce the study to potential participants and provide those interested and eligible with a research information pack. They will also collect contact details of those expressing an interest (for follow up by the research assistant). The research information pack contains a concise lay description of the study, contact details of the researchers, a hard copy questionnaire to establish baseline demographic details, consent form, and reply-paid envelope. The research assistant will contact all those provided with an information pack to discuss potential participation and answer any questions they may have. Those who agree to participate will complete the consent form and questionnaire and return these to the research coordinator in the reply-paid envelope provided. The research coordinator will record the date of receipt.

The research coordinator will randomize participants on receipt of the signed consent form. Participants will be randomized using a 1:1 ratio in balanced blocks and stratified by BMI and geographical setting. Allocation concealment will be assured through the use of a remote Web-based allocation service.

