### Sample Size

This trial is designed to detect a clinically significant increase in the proportion of women who have a gestational weight gain within the current IOM recommendations from 36% to 42%. A recent prospective study in Australia with 664 participants (of all BMI categories) found that 36% of the cohort gained within the range recommended by the IOM [43]. This is greater than the proportion found in the LIMIT trial (33%), though this trial included only overweight and obese women [18] who are known to be more at risk of excessive weight gain. A total sample size of 1156 (578 in each group) will allow detection of statistical significance with 80% power and two-sided 5% significance level [44].

The follow-up period is short in studies using GWG as the primary outcome, given the end point is birth. However, there is wide variation in reported drop-out and loss to follow-up rates, which range from 3% to 20% [18,45-47]. These are composed largely of women experiencing miscarriage, fetal loss, and moving out of area. Taking a conservative approach, we have allowed for a 15% drop-out rate, which gives a total recruitment target of 1330 women.

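### A recruitment target of 1330 does not allow for 15% drop-out from 1156 women; it covers 13.1%, a slip worth about one percentage point of power

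*Protocol article*

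**What the plan says.** The Sample Size section of the protocol article works in two steps. The first fixes the number needed for analysis: "A total sample size of 1156 (578 in each group) will allow detection of statistical significance with 80% power and two-sided 5% significance level". The effect to be detected is a rise from 36% to 42% in the proportion of women whose weight gain falls within the Institute of Medicine range. The second step inflates that number for losses: "we have allowed for a 15% drop-out rate, which gives a total recruitment target of 1330 women".

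The inflated figure is then used as the number to randomize. The Methods paragraph of the Abstract says the trial "will randomize 1330 women to control or intervention groups", and Study Design and Overview says "We will randomize 1330 pregnant women to the control and intervention groups". Allocation is 1:1 (Recruitment and Randomization), so 1330 means 665 per group.

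The Data Analysis section plans an intention-to-treat analysis that includes withdrawals and losses, with multiple imputation of missing values. The article states no other inflation rule and no rounding convention.

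**The concern.** An allowance for drop-out is meant to leave the required number of women with an observed outcome after the assumed share of recruits has been lost. The share is lost from those recruited, so the required number must be divided by one minus the rate. The stated target is what comes out if the required number is increased by 15% instead. That always gives too few, because 15% of the larger, recruited number is more than 15% of the smaller, required one.

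At stake is whether the recruitment target delivers the analysis set on which the power statement rests. As written, the sentence claims protection against a 15% loss that the target does not give.

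**Working it through.** **Inputs**, all from the Sample Size section except the allocation ratio (Recruitment and Randomization): 1156 required, 578 per group; drop-out 15%; target 1330; 36% versus 42%; two-sided 5% level; 1:1 allocation.

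**Step 1: reproduce the stated target.**
- Total: 1156 × (1 + 0.15) = 1329.4, rounded up to 1330.
- Per group: 578 × 1.15 = 664.7, rounded up to 665; 2 × 665 = 1330.

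Both routes give the stated figure exactly.

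**Step 2: the target that meets the stated aim.** N = n / (1 − d).
- Total: 1156 / 0.85 = 1360.
- Per group: 578 / 0.85 = 680.
- Difference from the stated target: 1360 − 1330 = 30 women, or 30 / 1330 = 2.3%.

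**Step 3: what 1330 delivers.**
- After a 15% loss: 1330 × 0.85 = 1130.5, so about 1130 women, 565 per group.
- Shortfall: 1156 − 1130 = 26.
- Largest loss that still leaves 1156: 1 − 1156 / 1330 = 0.131, or 13.1%.

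**Step 4: the effect on power.** For two proportions with n per group, using the pooled variance under the null hypothesis and no continuity correction:

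power = Φ{ [Δ√n − 1.96 √(2 p̄(1 − p̄))] / √(p₁(1 − p₁) + p₂(1 − p₂)) }

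Here Δ = 0.06 and p̄ = 0.39. So √(2 × 0.39 × 0.61) = 0.6898, 1.96 × 0.6898 = 1.352, and √(0.2304 + 0.2436) = 0.6885.
- n = 578: (0.06 × 24.042 − 1.352) / 0.6885 = 0.132, power 55.2%.
- n = 565: (0.06 × 23.770 − 1.352) / 0.6885 = 0.108, power 54.3%.

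The slip costs 55.2 − 54.3 = 0.9 percentage points.

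**Step 5: separate this from the base sample size.** The same method needs 1037 per group, 2074 in total, for 36% versus 42% at 80% power. The drop from 80% to 55.2% is therefore already present at the full 578 per group, before any woman is lost. The cost of the slip hardly depends on that other error. For 36% versus 44%, a difference at which 578 per group comes close to 80%, power goes from 79.4% at 578 to 78.4% at 565, again about one point.

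**The case against.** **Losses stay in the analysis.** Intention-to-treat with multiple imputation keeps every randomized woman in the analysis set, so it could be said that nobody is lost. This does not rescue the allowance. Imputation does not restore the information in an outcome that was never observed, and the Sample Size section itself inflates the target because of drop-out. It describes losses as largely miscarriage, fetal loss and moving away, where a weight in labor would generally not be available.

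**The article is a condensed account.** That would excuse an omission. Here the figures are stated and do not agree.

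**The formula is not shown.** True. That the number was multiplied is an inference, although 1330 matches to the last woman both in total and per group. The finding does not depend on it: 1330 less 15% is not 1156, whatever route was taken.

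**The difference is trivial.** This largely stands. Thirty recruits is 2.3% of the target, the power effect is about one point, and a covered loss of 13.1% still lies within the 3% to 20% that the section reports from other studies. No conclusion of the trial is likely to turn on it.

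**Two stronger readings are not supported.** A reader who sees 54% power at 565 per group might infer that the drop-out step cut power from 80% to 54%. It did not; all but about one point of that gap comes from the base number. A reader might also infer that 15% cannot be called conservative when the reported range runs to 20%. But 15% is in the upper part of the range, and the word need not mean the maximum. A 20% loss is not the rate the plan adopted, and even 1360 recruits would then leave 1360 × 0.80 = 1088, short of 1156. That scenario says nothing about how the 15% was applied.

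**Conclusion.** The sentence is wrong as written: on the article's own figures, 1330 recruits do not leave 1156 women after a 15% loss. They leave about 1130, and the target protects 1156 only up to 13.1%. The consistent target would be 1360.

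The error is certain but small: about 26 evaluable women and about one percentage point of power. This rests on reading 1156 as the number needed with an observed primary outcome, as its place before the drop-out step implies, on losses being equal in the two groups, and on an unadjusted comparison of two proportions.

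Moving to 1360 would make the drop-out step right but would not give 80% power for 36% versus 42%, because 1156 does not give it. That is a separate and far larger point.

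**What to change.** **If 1330 is kept:** amend the last sentence of Sample Size to say either that the target allows for about 13% loss (1330 × 0.87 = 1157) or that about 1130 women would be evaluable at 15% loss. Restate the power for whichever evaluable number is given. The Abstract and Study Design and Overview already carry 1330 and need no change. The cost is wording only.

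**If the base number is recalculated:** divide the new number by 0.85. For example, 2074 / 0.85 = 2440, whereas 2074 × 1.15 = 2385.1, or 2386 rounded up, would repeat the slip and fall 54 short. The new target must then replace 1330 in the Abstract, in Study Design and Overview and in Sample Size. The drop-out step itself adds no cost here beyond doing the division correctly. The cost of a larger trial belongs to the base sample-size decision, and is not slight, given the article's report of about 100 women recruited in roughly 12 months.

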### Ethics

The study received multi-site ethics approval from the ACT Health Human Research Ethics Committee (ETH.5.16.064). All potential participants will be supported to make an informed choice regarding joining the study and will be required to sign a consent form before enrolment. Consent includes consent to access the individual’s data from clinical databases at each participating hospital. Individual data will not be reported and participant confidentiality will be protected.

### Trial Status

Due to resource limitations, the Eating4Two mobile phone app was originally developed in the Android platform only. Over 4 months from October 2014 to February 2015, we attempted to recruit 80 women at one site only to determine study feasibility. Eligibility for the study included ownership of an android smartphone. Exclusion criteria included gestation greater than 18 weeks, multiple pregnancy, and preexisting clinical conditions including diabetes. A research assistant approached women waiting for antenatal appointments at the busiest antenatal clinics in the hospital and in the community, 2 days per week. The recruitment strategy aimed to avoid burdening already busy clinicians with the additional task of recruiting to the study.

**Figure 4 figure4:**
[figure not shown]
Feasibility study recruitment results. RA: Research Assistant.

Figure 4 illustrates the results of the recruitment. In this period, 157 women were approached and only 9 women were successfully recruited to the study. The majority of women who were ineligible were so because they owned an iPhone rather than Android. Almost 30% were ineligible due to stage of gestation. Over 75% of eligible women who expressed an interest and were provided with a research pack failed to return a signed consent form and baseline questionnaire and thus enroll into the study.

## Results

The project is currently recruiting though with a rate of 100 recruitments in approximately 12 months, recruitment is slower than expected. Additional funds are being sought to enhance recruitment through the employment of additional research assistants and a comprehensive advertising strategy.

## Discussion

### Principal Findings

This protocol aims to determine whether the use of the smartphone app Eating4Two is effective in assisting women to optimize GWG and improve birth outcomes. The intervention takes advantage of smartphone technology, addresses the problem of the limited health service resources available to meet an expanding area of need, and focuses on empowering women to manage their weight in partnership with their maternity care provider. In addition, it addressed the question of whether the intervention impacts differently women with varying levels of relative socioeconomic advantage and disadvantage.

Our feasibility study clearly identified problems in both the recruitment strategy and in the app platform. Although iOS (iPhones) is more popular with younger populations [48], both the Android and iOS providers dominate the field in Australia, and providing the app in both platforms will greatly increase study eligibility.

The recruitment strategy was also revised to involve a range of maternity care service providers including general practitioners, private obstetricians, employed obstetricians, and midwives. Most women visit their general practitioner to confirm their pregnancy, and this makes this group particularly important to ensure that women are recruited early to resolve the other main issue compromising eligibility of advanced gestation. Relying on clinicians can be a risky recruitment strategy as they are often busy and prioritize clinical care. There are, however, a number of strategies that will be employed to enhance the strategy including early engagement; study logo; and regular communication through a study newsletter, eg, acknowledging participation (with merit letters or certificates for example) and showing appreciation [49].

### Digital Preservation

During the trial period, the app will only be available to research participants only, though source coding and App content have been preserved. Researchers interested in replicating this trial will be invited to contact the researchers directly. Health care interventions such as the Eating4Two app must be evaluated carefully to ensure no harm is brought to the pregnant woman or fetus.

### Limitations

The study relies on self-reported height and weight to establish the BMI of participants in the intervention group. Maternity care providers usually calculate BMI at the first antenatal booking visit, and participants can correct these data within the application if necessary. Nonetheless, it is reliant on the accuracy of the participant’s entry. Total weight gain is established by subtracting the woman’s first recorded pregnancy weight from her recorded weight in labor, and we will be unable to vouch for the accuracy of the scales used in various antenatal and labor and birth settings. The quality of the scales used and the procedures for maintaining and calibrating them may vary. Although this may affect the results of the study, it is important to test methods that will be used in translating the intervention to service delivery if successful. Finally, this study does not include any follow-up of women to assess their longer-term weight change post birth.

### Conclusions

Many women gain excessive weight during pregnancy, and this causes problems for the index pregnancy and contributes to the burden of overweight and obesity in society, as excessive gestational weight is often retained postpregnancy. To date, research has focused on intensive interventions that are costly for health services and are unlikely to be sustainable. Few studies have examined the way that women from varying socioeconomic positions might receive interventions. Maternity caregivers are often also reticent about raising the issue of weight with women, even though gestational weight gain is a clinically important issue. The Eating4Two mobile phone app is an intervention that if shown to be effective could be scalable and cost-effectively implemented throughout Australia.

## Abbreviations

ACT: Australian Capital Territory
BMI: body mass index
GWG: gestational weight gain
IOM: Institute of Medicine
SMS: short message service
IRSAD: Index of Relative Socioeconomic Advantage and Disadvantage
